### **Physical activity**

- *International Physical Activity Questionnaire – Short Form (IPAQ-SF)* (Craig et al., 2003): this is an extensively used self-report measure for physical activity during the past seven days. It provides us with a categorical score of physical activity, distinguishing between low, moderate and high levels of physical activity.

- *Actigraph accelerometer at hip (Barnett et al., 2016)*: this is an objective measure of physical activity level, frequently used in physical activity studies with older adults. Participants will be asked to wear this accelerometer during seven days (day and night). They will be asked to register when and why they did not wear the device in a personal diary provided by the researchers. The duration spent in moderate-to-vigorous PA (based on the cutpoints of Barnett et al. (2016)) will be used as an outcome in this study.

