### 6.3. Populations for analyses

The data set will be analysed according to the ‘intention to treat’ (taking into account everyone who was assigned to an intervention arm) and ‘per protocol’ (taking into account only those who received  $\geq 75\%$  of the intervention, and the control group) principle.

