#### Primary outcome

For each cognitive test used, a selection of outcome measures will be used based on literature. Next, composite scores will be constructed for short-term memory (STM), long-term memory (LTM), executive functioning (EF) and processing speed (PS). The procedure for this is described below

The outcome measures, categorized by cognitive function:

| Short-term memory (STM)                           | Long-term memory (LTM)                          | Executive functioning (EF)                             | Processing speed (PS)        |
|---------------------------------------------------|-------------------------------------------------|--------------------------------------------------------|------------------------------|
| VRM free recall distinct stimuli (VRMFRDS)        | VRM delayed recognition total correct (VRMDRTC) | SWM strategy (SWMSX)                                   | RTI reaction time (RTIFMDRT) |
| VRM immediate recognition total correct (VRMIRTC) |                                                 | SWM between errors levels 4, 6, 8 and 12 (SWMBE46812)* |                              |
| PAL first attempt memory score (PALFAMS28)        |                                                 | OTS problems solved upon first choice (OTSPSFC)        |                              |
| PAL total errors (PALTEA28)                       |                                                 |                                                        |                              |
| DMS percentage correct (DMSPCAD)                  |                                                 |                                                        |                              |

\*SWMBE46812 is calculated by summing SWMBE4, SWMBE6, SWMBE8, SWMBE12

*STEP 1:* Create z-scores based on the pooled mean (across conditions), separately for each time point

*STEP 2:* Reverse-score the z-scores for the following outcome measures:

PALTEA

SWMSX

SWMBE46812

RTIFMDRT

*STEP 3:* Calculate the composite scores using the following formulas

$STM = (VRMDRDS + VRMIRC + PALFAMS28 + PALTEA28 + DMSPCAD)/5$

$LTM = VRMDRTC$

$EF = (SWMSX + SWMBE46812 + OTSPSFC)/3$

$PS = RTIFMDRT$

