The outcomes are measured repeatedly at different time points, and are nested within individuals. This implies our data has a two-level structure, and this calls for an analysis technique taking into account the correlation between observations from the same person (Hoffman & Walters, 2022). Therefore, linear mixed models with random intercepts will be used, to take into account that each individual participant has a different starting point. Time (baseline, 3m, 6m and 12m) and condition (PA+CA, PA only, CG), and their interaction will be included as fixed effects.

Models with different levels of adjustment will be run: (1) crude model, (2) partially adjusted model including age, sex and education as covariates, and (3) fully adjusted model including age, sex, education, baseline PA and baseline CA as covariates. Model fit indices will be used to choose the models with the best fit.

In case of significant effects, post-hoc pairwise comparisons will be conducted to examine differences in the estimated marginal means of the outcome at T0, T1, T2 and T3 between 1) WALK+ vs. WALK-only and 2) WALK+ vs. CONT, but also the changes from T0 to T1, T0 to T2, T0 to T3, T1 to T2 and T2 to T3 for each group (WALK+, WALK-only and CONT). The p-values will be corrected for multiple testing.

The analysis will be conducted for the intention-to-treat and per protocol populations.

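### If any baseline activity value is missing, the fully adjusted ITT model omits that participant and its fit index can no longer be compared with those of the other models

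*Combined protocol and SAP*

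**What the plan says.** Section 6.4, Primary outcome, states that "linear mixed models with random intercepts will be used", with time (four visits), condition and their interaction as fixed effects. Three versions are to be run: crude; adjusted for age, sex and education; and a third, given together with the rule for choosing between them: "fully adjusted model including age, sex, education, baseline PA and baseline CA as covariates. Model fit indices will be used to choose the models" that fit best. No index is named.

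The analysis is run for the intention-to-treat (ITT) and per-protocol populations. Section 6.3 defines ITT as "taking into account everyone who was assigned to an intervention arm".

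Baseline CA is the CLAS questionnaire (section 5.1). The plan does not say whether baseline PA is the seven-day accelerometer measure or the IPAQ-SF. For the accelerometer, participants keep a diary: "They will be asked to register when and why they did not wear the device". Section 6.4 names a wear-time algorithm but gives no minimum valid wear.

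Outcomes are standardised: "Create z-scores based on the pooled mean (across conditions), separately for each time point".

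The plan contains no rule for missing covariates, no imputation method, and no requirement that the three models use the same participants.

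**The concern.** A likelihood-based mixed model copes with missing outcomes but not with missing covariates. If a time-constant covariate is missing and nothing is imputed, every visit of that participant leaves the likelihood. Only the fully adjusted model needs baseline PA and CA, so only that model can lose people for this reason. Two things follow if even one value is missing.

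- The fully adjusted ITT result no longer covers everyone assigned.
- The fit comparison is invalid. The log-likelihood is a sum over the observations used, so a model fitted to fewer people can score better whether or not activity predicts cognition.

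The rule that picks the model for the primary result would then tend to favour the one model that can leave out randomised participants.

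**Working it through.** **Starting figure.** The plan gives no figure for missing covariates. Its ITT denominator is 149, which reproduces as 124 x 1.20 = 148.8, rounded up. (Dividing instead, 124/0.80, gives 155; that is a separate matter.)

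**Assumed inputs, not in the documents.** Share missing baseline PA or CA: one person, 5% or 10%. Outcome SD: 0.5 to 1.0. Intraclass correlation (ICC): 0.5 to 0.7, with a wider range where shown. Four complete visits per person.

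**Bounds on the SD from the plan's scaling.** Long-term memory and processing speed are single z-scores, so their SD is 1 at each visit. Short-term memory averages five z-scores and executive functioning three. If the items are not negatively correlated, their SDs are at least 1/sqrt(5) = 0.447 and 1/sqrt(3) = 0.577.

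**-2 log-likelihood (-2LL) per person,** with equal correlation between visits and before covariate adjustment:

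-2LL = 4 ln(2π) + 8 ln(SD) + 3 ln(1 - ICC) + ln(1 + 3 ICC) + 4

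- SD 1, ICC 0.5: 7.35 + 0 - 2.08 + 0.92 + 4 = 10.2
- SD 0.73, ICC 0.6: 7.35 - 2.52 - 2.75 + 1.03 + 4 = 7.11
- SD 0.5, ICC 0.7: 7.35 - 5.55 - 3.61 + 1.13 + 4 = 3.3
- SD 0.5, ICC 0.8: 2.2
- SD 0.3, ICC 0.6: about 0
- SD 0.24, ICC 0.5: -1.2 (artefact reversed)

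At SD 1 the value stays between 10.2 and 5.8 for ICC 0.5 to 0.9. At the short-term memory floor of 0.447 it runs from 3.8 (ICC 0.5) to 1.3 (ICC 0.8), and is slightly negative (-0.7) at ICC 0.9.

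**Against the AIC penalty.** Two extra coefficients cost 2 x 2 = 4. (If baseline PA were the three-level IPAQ-SF category, there would be three extra coefficients and a cost of 6.) Two covariates with no true effect lower -2LL by 2 on average. With m people omitted, the expected AIC gain of the fully adjusted model is therefore m x (-2LL per person) + 2 - 4.

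- SD 1, ICC 0.5: m = 1 gives 10.2 - 2 = 8.2; m = 7 gives 7 x 10.19 - 2 = 69.3.
- SD 0.7, ICC 0.6 (6.78 per person): 4.8 and 45.5.

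**Simulation of the planned model** (maximum likelihood, 149 people, four visits, 400 trials per setting, activity with no true effect). AIC gain of the fully adjusted model on the reduced sample over the partially adjusted model on all 149, with the share of trials choosing the fully adjusted model:

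| SD, ICC | 1 missing | 5% (142 left) | 10% (134 left) |
|---|---|---|---|
| 1, 0.5 | 8.3 (100%) | 69.1 (100%) | 151.9 (100%) |
| 0.7, 0.6 | 5.1 (98%) | 45.0 (100%) | 100.9 (100%) |
| 0.5, 0.8 | 0.3 (49%) | 13.8 (98%) | 31.1 (100%) |

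With both models fitted to the same people, the fully adjusted model averages about 2 points worse and is chosen in about 12-18% of trials; theory gives exp(-2) = 13.5%.

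With activity truly prognostic (0.15 SD per covariate) and 5% missing, the unequal-sample gain is about 76 points, of which about 7 remain on a common sample.

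**Coverage and precision.** 149 x 0.05 = 7.45 and 149 x 0.10 = 14.9, so about 7 to 15 people, or 28 to 60 visits, are lost. The standard error grows by 1/sqrt(0.95) = 1.026 to 1/sqrt(0.90) = 1.054.

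**The case against.** The strongest reply is that nothing in the plan deletes anyone. It is silent, deletion is what a mixed model does by default, and with complete baseline data the problem is nil. This stands as a limit on certainty. Section 2 discloses allocation only once baseline measurement is complete, and section 5.3 places the questionnaires at the baseline visit, so a missing CLAS may be rare. A non-wear diary also does not show that baseline values will be missing: partial non-wear yields no missing value unless a valid-wear rule makes it one. But at SD 1 a single missing participant is enough to tip AIC, so a low rate does not remove the point.

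A reader might infer three stronger things that the documents do not support.

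- *That the fully adjusted model would fit better only because people are missing.* Part of the gain can be genuine, and the artefact shrinks or reverses at small variance. A participant with fewer than four visits also contributes less.
- *That those omitted are the people who did not wear or return the device.* This holds only if baseline PA is the accelerometer measure, which the plan does not say.
- *That the arm comparison is biased.* Baseline values are collected before allocation is known, so their loss should not depend on knowledge of the arm.

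It is also fair to say that all three models are to be run, that the crude and partially adjusted models need no activity values, and that the covariate lists for the secondary outcomes omit baseline PA and CA. The problem is therefore confined to the fully adjusted primary model and the rule that chooses it.

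**Conclusion.** The point holds conditionally. If any participant lacks baseline PA or CA, applying the stated rule without imputation gives a fully adjusted ITT result that does not cover everyone assigned, and compares fit indices that are not comparable.

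The artefact is about 3 to 10 points of -2LL per omitted participant for SD 0.5-1.0 and ICC 0.5-0.7, against an AIC penalty of 4. It is most dependable for long-term memory and processing speed, where the plan's scaling sets the SD at 1. It is weaker for composites with low SD and high ICC. The missing share, the ICC, the composite SDs and the use of AIC are assumptions; the documents give none of them.

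The harm is lost coverage, a modest loss of precision (standard errors about 3-5% wider at 5-10% missing) and an invalid model choice. It should be corrected before analysis, and the correction is small.

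**What to change.** Amend section 6.4, Primary outcome, to state that:

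1. Missing baseline covariates are imputed from other baseline variables only, pooled across arms and without post-baseline outcomes. Every randomised participant with at least one cognitive score then stays in all three models. Because CANTAB is given at baseline, this should keep nearly everyone.
2. Fit indices are named, and are compared only on that common set under maximum likelihood. Alternatively, one primary adjusted model is named in advance, which removes the comparison altogether. If the named model is the fully adjusted one, item 1 is still needed.
3. Baseline PA is identified as the accelerometer measure or the IPAQ-SF. If it is the accelerometer, the minimum valid wear is given, since without it the amount missing cannot be determined.

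The cost is a few sentences and a few lines of code. Imputation slightly attenuates the coefficient of the imputed covariate; because arm is randomised, this does not bias the contrast between arms.

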### 6.4. Statistical analyses

#### General

For descriptive statistics, categorical data will be presented as percentages and counts, continuous data will be presented as means with standard deviations or medians with interquartile range in case of non normally distributed data.

For inferential statistics,  $\alpha$  will be set at 0.05, and 95% confidence intervals will be calculated. In case of multiple testing, a correction of the p-values will be used.

Covariates will be specified below and are selected based on theoretical knowledge.

Checks of assumptions will be performed, in case of non-normality, transformations of the variables or non-parametric tests will be used.

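### No single primary analysis is fixed: an unnamed fit index picks the covariates, ITT and per-protocol are unranked, and per-protocol contrasts with control are not randomised

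*Combined protocol and SAP*

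**What the plan says.** Section 6.4 (Primary outcome) analyses four cognitive composites with a random-intercept mixed model containing time, condition and their interaction. It sets out three levels of adjustment: "Models with different levels of adjustment will be run: (1) crude model, (2) partially adjusted model including age, sex and education as covariates", and thirdly a "fully adjusted model including age, sex, education, baseline PA and baseline CA as covariates". The data then decide among them: "Model fit indices will be used to choose the models with the best fit". The section does not state the index, the estimation method (ML or REML), or whether one choice serves all four composites.

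The same section ends: "The analysis will be conducted for the intention-to-treat and per protocol populations". Section 6.3 defines the per-protocol set as those who received at least 75% "of the intervention, and the control group". Walking-arm participants are filtered on what they received; controls are not filtered. Neither section says which population decides.

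On error control, Section 6.4 (General) says that alpha "will be set at 0.05, and 95% confidence intervals will be calculated", and adds: "In case of multiple testing, a correction of the p-values will be used". Nothing says that this correction spans the two populations.

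If effects are significant, Section 6.4 compares the enriched arm with each of the other two arms on marginal means at each visit, and examines change over time within each arm. Section 2 stratifies randomisation by location and by availability (two scheduling options per location). Neither factor appears in any of the three models.

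**The concern.** A confirmatory result needs one model and one population fixed in advance. Here the covariate set depends on an index still to be chosen. Fit indices can be compared only between models fitted to the same people and, where the fixed effects differ, under ML; the plan secures neither condition. If ITT and per-protocol disagree, the plan does not say which is the trial's answer.

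The per-protocol set is the more serious part. Attendance is decided after randomisation and may well follow health and motivation. Filtering the walking arms and not the controls compares a selected group with an unselected one. Section 6.1 states the primary hypothesis against both other conditions, so the contrast with control is part of the primary claim. Section 4 itself expects attendance to vary.

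**Working it through.** The plan gives no figure of its own on this point. The planning effect of 0.30 (Section 6.2) serves only as a scale.

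**1. Results left open.** Three covariate sets × 2 populations = 6 fits per composite. If the fit rule is followed, one covariate set remains in each population: 1 × 2 = 2 results per composite.

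**2. Does choosing by fit raise the type I error?** Two simulations under no effect were run.
- 40 per arm, 3,000 runs: prespecified full model 4.6%, AIC-selected model 4.7%. The Monte Carlo standard error is √(0.05 × 0.95 / 3,000) = 0.4 percentage points.
- The Section 6.4 model with 149 participants, 1:1:1, four visits, 20% random dropout and 2,000 runs per scenario (standard error about 0.5 points). Assumptions not in the documents: two-sided tests; intraclass correlation 0.6; covariates explaining 30% of between-person variance; 50% or 75% of walkers reaching the threshold; attendance correlated 0 to 0.5 with cognitive level and trend. For the joint time × condition test in ITT, the error was 0.046-0.059 with the full set fixed and 0.046-0.059 with AIC choice. Crude and full estimates of the 6-month change correlated at 0.998.

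One limit applies: AIC took the full set in 1,981 to 1,989 of 2,000 runs in the second simulation, so there was little real selection in that setting.

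**3. Leaving the population open** (second simulation, AIC-chosen covariates, chance that at least one population is significant).
- Joint test: 0.069-0.094.
- 6-month marginal mean, enriched arm versus control: 0.067-0.090 if attendance is unrelated to cognition, rising to 0.310 at correlations of 0.5 with 50% reaching the threshold. ITT with the full set fixed gave 0.045-0.061. The upper end reflects bias in the per-protocol contrast, not multiplicity.

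**4. Per-protocol bias against control at one visit.** Let p be the share of walkers reaching 75%, and g the prognostic gap between those who do and those who do not. With no treatment effect, controls have the mean of the whole randomised group, so

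bias = m_adherers − [p × m_adherers + (1 − p) × m_others] = (1 − p) × g.

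| p (assumed) | g in SD (assumed) | (1 − p) × g | divided by 0.30 |
|---|---|---|---|
| 0.80 | 0.2 | 0.04 | 13% |
| 0.80 | 0.4 | 0.08 | 27% |
| 0.50 | 0.2 | 0.10 | 33% |
| 0.50 | 0.4 | 0.20 | 67% |

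The last column reads 0.30 as SD units, which Section 6.2 does not state.

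**5. Change from baseline.** A gap that is constant over time cancels: (1 − p) × g − (1 − p) × g = 0. Only a gap in trend remains. In the second simulation, the spurious per-protocol difference at 6 months (fully adjusted model) was about 0.01-0.32 SD for marginal means and about 0-0.10 SD for change.

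**6. What 75% could mean.** Section 4 gives 24 weeks × 2 = 48 group sessions, plus 24 × 1 = 24 encouraged individual sessions, 72 in all. The threshold is 0.75 × 48 = 36 or 0.75 × 72 = 54 sessions, depending on what counts.

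**The case against.** The strongest reply is that most of this is prespecified. Section 6.4 (General) chooses covariates on theory, the three sets are listed, fit selects among them, and the ITT result must be produced in any case. The model's central test is time × condition, where a constant prognostic gap cancels, and visit-level comparisons follow only after a significant result. The added value of enrichment (Section 1) rests on enriched versus plain walking, where both arms face the same filter.

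Much of this stands, and it rules out several stronger readings.
- A reader might infer six competing primary results. The fit rule leaves two.
- A reader might infer that choosing by fit inflates the type I error. AIC choice did not do so in either simulation. Taking the smallest p-value of the three models gave 7.8% in the first simulation, but the plan describes no such procedure.
- A reader might apply the 13-67% range to the whole primary analysis. It concerns visit-level marginal means against control only.
- Theory choosing the candidates and fit choosing among them is not a contradiction. Nor do the documents say that the choice is made separately per composite, or that people with missing baseline covariates are dropped.

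Three things remain. Producing both populations does not say which one decides. An unnamed index does not determine a model. And the significance gate does not say which effect must be significant, while the between-group comparisons behind it are the visit-level means, where the bias is largest.

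**Conclusion.** The concern holds in a limited form. Two primary results per composite are open because the populations are unranked, and the covariate set within each is not determined because no index is fixed. As written, the per-protocol contrasts with control are not randomised comparisons. That follows from the definition in Section 6.3 and needs no assumption.

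The direction and size do need assumptions. The bias favours the intervention if attenders have the better prognosis. It is 0.04-0.20 SD in visit-level marginal means for 50-80% adherence and a gap of 0.2-0.4 SD, and smaller for change from baseline (about 0-0.10 SD in simulation). The documents give neither the adherence share nor the gap. The one-sided filter does not touch enriched versus plain walking. The case for change rests on the unfixed index and the unranked populations, not on any error inflation from AIC.

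**What to change.** In Section 6.4, name one primary analysis for all four composites: the ITT mixed model adjusted for age, sex, education and the randomisation strata (location and availability). Delete the fit-index sentence and report the crude and fully adjusted models as sensitivity analyses.

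In Section 6.3, label per-protocol as supportive and unable to override ITT, and state that its contrasts with control are not randomised comparisons. Define what counts towards the 75%: group sessions only, or individual sessions as well.

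A complier-average estimate with 75% as receipt may look like the natural replacement, but it assumes no effect below the cut. Suppose the effect is linear in dose, 0.30 at full attendance, with half attending 90% and half 50%. Then ITT = 0.30 × (0.5 × 0.9 + 0.5 × 0.5) = 0.21 and the complier estimate is 0.21 / 0.5 = 0.42. The true effect above the cut is 0.30 × 0.9 = 0.27, so benefit is overstated by 0.15. It should not be adopted in that form.

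The cost is mainly wording. The sample size does not change. Two locations × two options make four strata, so adjustment uses up to 3 degrees of freedom. The per-protocol result becomes less prominent. With ITT and the fully adjusted set fixed, the second simulation held the error at 0.046-0.059 (joint test) and 0.045-0.061 (6-month marginal mean). The proposed covariate set with strata was not itself simulated.

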#### Secondary endpoints:

We hypothesize that both the cognitively enriched walking program and the walking program without cognitive enrichment will have more beneficial effects on moderate-to-vigorous PA levels compared to the control group.

We hypothesize that both the cognitively enriched walking program and the walking program without cognitive enrichment will have more beneficial effects on psychosocial wellbeing compared to the control group.

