### **Secondary outcomes**

For physical activity, the Choi et al. (2011) algorithm will be used to define (non-)wear time. Next, the cutpoints of Barnett et al. (2016) will be used to determine time spent in moderate-to-vigorous physical activity.

Other outcomes will be processed as indicated in their corresponding manuals.

The same analysis as for the primary outcome will be used. The only difference will be the covariates: for physical activity these will be age and sex, for psychosocial wellbeing these will be age, sex and civil status.

The analysis will be conducted for the intention-to-treat and per protocol populations.

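### For MVPA and psychosocial wellbeing both walking arms are hypothesised to beat control, but no walking-only versus control contrast is planned after baseline

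*Combined protocol and SAP*

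**What the plan says.** Section 6.1 (Secondary endpoints) states two hypotheses. Each has as its subject "both the cognitively enriched walking program and the walking program without cognitive enrichment". The first predicts "more beneficial effects on moderate-to-vigorous PA levels compared to the control group"; the second predicts "more beneficial effects on psychosocial wellbeing compared to the control group".

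Section 6.4 (Primary outcome) fits a linear mixed model in which time, "condition (PA+CA, PA only, CG), and their interaction will be included as fixed effects". If effects are significant, pairwise comparisons of estimated marginal means follow at T0, T1, T2 and T3. The arm pairs are numbered: "between 1) WALK+ vs. WALK-only and 2) WALK+ vs. CONT". The other planned comparisons are five changes over time, "for each group (WALK+, WALK-only and CONT"), all of them within one arm.

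Section 6.4 (Secondary outcomes) then says: "The same analysis as for the primary outcome will be used. The only difference will be the covariates".

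The labels WALK+, WALK-only and CONT are not defined. I read them as PA+CA, PA only and CG, the only mapping that makes sense.

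**The concern.** The numbered pairs fit the primary hypothesis, which sets enriched walking against each of the other two arms. They do not fit the secondary hypotheses, which set each walking arm against control. The carry-over sentence names covariates as the sole change, so it leaves no room to assume a different contrast set for the secondary outcomes.

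Followed as written, the plan gives no direct between-arm result on whether group walking without enrichment improves activity or wellbeing relative to no programme. That is half of each secondary hypothesis. The report might then lean on a change in the walking-only arm beside a lack of change in the control arm, which is not a comparison of the two. If the contrast is added once results are known, whether it belongs in the corrected family is left to the analyst.

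**Working it through.** No stated figure has to be reproduced, because the point is one of matching text to text.

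**Step 1: needed against planned.** Three arms give three pairs.

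| Pair | Needed by the secondary hypotheses (6.1) | Listed in 6.4 |
|---|---|---|
| WALK+ vs CONT | yes | yes |
| WALK-only vs CONT | yes | no |
| WALK+ vs WALK-only | no | yes |

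Each secondary hypothesis needs 2 pairs, and 1 of them is planned. The remaining planned pair matches no stated secondary hypothesis.

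**Step 2: visits.** The plan lists contrasts at four time points. Section 2 says allocation is disclosed only after baseline measurement, so a T0 contrast cannot show a programme effect. That leaves 4 − 1 = 3 informative visits. Section 6.1 names no visit for these hypotheses, so 3 missing contrasts per outcome is an upper bound.

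**Step 3: outcomes.** The hypotheses cover MVPA and psychosocial wellbeing. Section 5.1 lists five psychosocial instruments (BDI-II, WEMWBS, De Jong Gierveld, SSL 12-I, ERA-12). Counting one score per instrument, at most (1 + 5) × 3 = 18 contrasts are missing in each analysis population.

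**Step 4: other places where the contrast might be supplied.** The baseline comparison at the end of section 6.4 covers all conditions, but only at baseline. The within-arm changes number 5 × 3 = 15, and none is between arms. No other section adds walking-only versus control.

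**Step 5: what the planned output yields anyway.** At a given visit let A = WALK+ − WALK-only and B = WALK+ − CONT. Then B − A = WALK-only − CONT, so the point estimate can be recovered. Its variance is Var(A) + Var(B) − 2Cov(A,B), and the covariance is not part of the planned output. As an illustration, assume independent arm means with equal variance v, which is reasonable under 1:1:1 allocation with similar dropout. Then Var(A) = Var(B) = 2v, Cov(A,B) = v, and Var(B − A) = 2v + 2v − 2v = 2v. The missing contrast would be as precise as the listed ones, but its interval has to be taken from the fitted model.

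**Step 6: multiplicity after the fix.** The plan names no correction method, so Bonferroni within a visit is assumed here.

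- Two corrected contrasts per visit: 0.05/2 = 0.025.
- Three corrected contrasts per visit: 0.05/3 = 0.0167.

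For the power cost, take the planned 124 evaluable participants, 124/3 ≈ 41.3 per arm, a simple two-sample comparison, and power ≈ Φ(d√(n/2) − z) with z the two-sided critical value. The values of d are assumed.

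| d | α = 0.025 | α = 0.0167 | Loss |
|---|---|---|---|
| 0.3 | 0.190 | 0.151 | 0.039 |
| 0.5 | 0.513 | 0.452 | 0.061 |
| 0.6 | 0.687 | 0.631 | 0.056 |
| 0.8 | 0.919 | 0.893 | 0.026 |

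Keeping all three pairs in the corrected family costs about 3 to 6 percentage points per contrast. Replacing one pair by the other costs nothing.

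**The case against.** The strongest reply is that the information is already in the model. Condition has three levels, so the condition and condition-by-time tests include walking-only and control, and the point estimate comes out by subtraction (Step 5). The arms, comparator and direction are fixed in section 6.1, so adding the contrast completes a stated hypothesis and does not invent one. The plan itself treats all pairwise comparisons as follow-up to a significant model effect.

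Most of this stands, and it limits the point. A reader might infer that within-arm change would be the only evidence on walking alone, or that any later contrast would be purely data-driven. The documents support neither reading. What the reply does not supply is a result for the hypothesis itself. A three-arm test does not say which arm differs or in which direction, and a subtracted estimate has no planned interval or corrected p-value. Stating the hypothesis in 6.1 does not settle whether its test is inside the correction.

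It is also tempting to count four missing contrasts per outcome, or to extend the point to every secondary outcome. The first counts baseline. The second goes beyond section 6.1: the CFQ, the IPAQ-SF category and the PROMIS general health and sleep scores carry no stated hypothesis of superiority over control.

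**Conclusion.** Wrong as written, for MVPA and the psychosocial measures only. The walking-only half of each secondary hypothesis has no planned between-arm test, confidence interval or corrected p-value at 3, 6 or 12 months: 1 of 2 needed pairs, at up to 3 visits per outcome. This rests on reading the numbered pairs as a complete list and the carry-over sentence literally.

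A reader might go further and conclude that the trial cannot address walking alone, or that the main result is at risk. Neither follows. The contrast can be estimated from the planned model without new data, and the two listed pairs match the primary hypothesis exactly. I rate it should-fix.

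**What to change.** In section 6.4 (Secondary outcomes), add a sentence to this effect: for MVPA and psychosocial wellbeing, the between-arm contrasts at 3, 6 and 12 months include WALK-only vs CONT as well as WALK+ vs CONT, each reported with a confidence interval, and both are included in the multiplicity correction. Amend the statement that only the covariates differ so that the two agree, and map the WALK labels to the arm names used elsewhere.

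The plan should also say where WALK+ vs WALK-only stands for these outcomes. Consistency with section 6.1 requires only the addition; demoting the third pair is a choice for the team. Reported as exploratory outside the corrected family, it leaves the corrected count at 2 per visit. Kept inside, it raises the count from 2 to 3, with the modest power cost shown above. It is therefore not safe to say that the change adds no multiplicity without stating which option is taken.

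The cost is a sentence or two of SAP wording, with no new data, visits or participants. It should be settled before outcome data are examined.
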